### Interim analyses {21b}

There is no plan of conducting an interim analysis in this study.

### Methods for additional analyses (e.g., subgroup analyses) {20b}

We plan to conduct subgroup analysis based on disease burden/history and social factors including co-existing cardiovascular diseases, undernutrition, and social situation (e.g., living alone). It is expected that individuals with COPD and coexisting cardiovascular diseases or undernutrition deviate from individuals with COPD but without these conditions. Subgroup analyses will be carried out using linear or logistic mixed-effects models that include an intervention group-subgroup-time three-way interaction as a fixed-effects and randomization blocks and participants as random (intercept) effects. Subgroup effects will be reported as estimated mean differences of differences in changes from baseline to 3 months accompanied by the corresponding 95% confidence intervals and *p* values.

### Methods in analysis to handle protocol non-adherence and any statistical methods to handle missing data {20c}

#### Missing outcomes values

For the primary outcome missing outcome values will be addressed using three approaches. We will consider two approaches that use imputation, making different assumptions about participants with missing data: 1) HRQoL remains unaltered (corresponding to last observation carried forward) and 2) HRQoL deteriorates over time with a rate of 2.5% or 5% per month to a maximum deterioration of 10 and 20%, respectively. The argument for the second approach is that it is expected that the main reason for missing data will be the worsening of COPD or other comorbidities or the detection of new conditions. The first and second approaches make explicit assumptions about the missingness mechanism, which is assumed to be missing not at random. For both approaches, multiple imputations will be applied to accommodate the uncertainty related to imputing missing data and Rubin’s rule will be applied to obtain standard errors [44]. The third approach will be fitting mixed models without any imputation, using all available data (an available-case analysis), corresponding to assuming the missingness mechanism is missing at random (optimistically assuming that participants dropping out or with missing data of other reasons will have similar trajectories after drop-out/event causing missing data as the other participants). The two imputation approaches will produce estimates that may be used for evaluating effectiveness whereas the third approach will produce efficacy estimates.

For the secondary outcomes, missing outcome values will be handled in the same way as the primary outcome: (1) secondary outcomes remain unaltered after drop-out (corresponding to the last observation carried forward), and (2) weight, BMI, fat-free mass, fat mass, functional capacity (stand chair test and grip strength), and disease-related quality of life deteriorate over time with a rate of 2.5 or 5% per month to a maximum deterioration of 10 and 20%, respectively. The secondary outcomes related to hospital contacts will increase over time by 2.5 and 5% per month to a maximum of 10 and 20%, respectively. For the secondary outcomes, available-case analyses will also be carried out.

For the other outcomes, only the last observation carried forward and available-case analyses will be carried out.

Intermittent missing outcome values occurring at the 1-month visit will not be imputed.

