### Sample size {14}

In our study, the primary outcome, HRQoL, is measured using the EuroQoL EQ-5D-5L questionnaire. However, our sample size is calculated based on results from a Japanese study investigating the effect of nutritional support combined with exercise on several outcomes including HRQoL measured using the chronic respiratory disease questionnaire among stable COPD patients. The chronic respiratory disease questionnaire consists of four domains (dyspnea, fatigue, emotional, and mastery) with 20 items in total. Each item is scored on a 7-point scale. There are no reports of a clinical relevant change/difference in the total HRQoL score of the chronic respiratory disease questionnaire. In the Japanese study, a 10-point higher total HRQoL score was reported in the intervention group compared to the control group (109 vs. 99, *p* = 0.04) at the end of the intervention with a standard deviation of 17 points [24] as used in our sample size calculation. With an estimated drop-out rate of 20%, the inclusion of 60 participants in each group, will provide a power of 0.8 at a significance level of 0.05.

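### The decline scenarios for missing EQ-5D-5L values are not varied by arm, so they do not test informative drop-out that differs between arms

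*Protocol article*

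**What the plan says.** Section {20c} of the Protocol article, under Missing outcomes values, names three approaches for the primary outcome:

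- The first assumes that "HRQoL remains unaltered (corresponding to last observation carried forward").
- The second assumes that "HRQoL deteriorates over time with a rate of 2.5% or 5% per month", with ceilings of 10% and 20%.
- On the third it says: "The third approach will be fitting mixed models without any imputation, using all available data (an available-case analysis"). This one assumes missing at random (MAR), and the article itself calls that optimistic.

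The two imputation approaches are introduced as "making different assumptions about participants with missing data", with no split by arm, and the article adds: "The first and second approaches make explicit assumptions about the missingness mechanism, which is assumed to be missing not at random". The reason given for the decline is an expectation that "the main reason for missing data will be the worsening of COPD or other comorbidities". The same section assigns the imputed analyses to effectiveness and the mixed model to efficacy, and section {8} describes the trial as an effectiveness trial.

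Section {14} plans drop-out as one overall figure: "With an estimated drop-out rate of 20%, the inclusion of 60 participants in each group".

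**The concern.** A proportional decline applied to all drop-outs lowers both arms. What reaches the arm difference is mainly the imbalance in drop-out multiplied by the decline. If the arms lose similar shares of participants, the 0%, 2.5% and 5% scenarios give nearly the same difference whatever happened to those who left. Three agreeing rows in a results table could then be read as robustness.

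One scenario is absent: drop-outs faring worse in one arm than in the other. It is plausible here. The trial is open-label (section {17a}). Only the intervention arm receives regular telephone contact, a nutritional plan and a daily weight diary (section {11a}), so the reasons for leaving, and the course afterwards, may differ by arm. At stake is what a positive primary result may claim about missing data, above all in the imputed analyses on which the effectiveness statement is to rest.

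**Working it through.** **The plan's own figure.** Section {14} gives a difference of 10 points, SD 17, power 0.8 and alpha 0.05 (taken as two-sided) on the chronic respiratory disease questionnaire.

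- n per arm = 2 × (1.960 + 0.842)² × 17² / 10² = 45.4, so 46. Dividing by 0.8 gives 57.5, so 58. The t-based version gives 47, then 59.
- The stated 60 per group is consistent with this.
- The standardised effect is 10/17 = 0.588.

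**Decline by 3 months.** 3 × 2.5% = 7.5% and 3 × 5% = 15% for someone who leaves just after baseline. The ceilings of 10% and 20% would be reached only at 4 months, so they do not bind.

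**Assumptions not in the documents.** Mean EQ-5D index M of 0.6 to 0.8; SD 0.20; the standardised effect carried over to EQ-5D (0.588 × 0.20 = 0.118); drop-out before month 1; drop-outs' last values near M in both arms.

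**Formula.** With drop-out shares p1 (intervention) and p0 (control) and proportional declines D1 and D0, the shift in the arm difference relative to LOCF is −(p1 × D1 − p0 × D0) × M.

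- Common decline D, as planned: −(p1 − p0) × D × M.
- Decline in intervention drop-outs only: −p1 × D1 × M.

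**20% drop-out in each arm.**

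- MAR difference 0.118; LOCF 0.80 × 0.118 = 0.094.
- Common decline of 15%: −(0.20 − 0.20) × 0.15 × M = 0.000, so the difference stays at 0.094.
- Intervention-only decline of 15%: −0.20 × 0.15 × 0.6 = −0.018, giving 0.076; with M = 0.8, −0.024, giving 0.070.
- If drop-outs instead leave after month 1 with half the effect gained, two months of common decline shift the difference by −0.20 × 0.10 × 0.059 = −0.001. The near-zero result does not depend on very early drop-out.

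**Unequal drop-out, common decline of 15%.**

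- 25% intervention, 15% control: −0.10 × 0.15 × M = −0.009 (M = 0.6) to −0.012 (M = 0.8).
- 30% and 10%: −0.018 to −0.024.
- 10% and 30%: +0.018 to +0.024.

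**Simulation.** 60 per arm, 4,000 runs per setting, true effect 0.10, mean 0.6, SD 0.20, baseline-to-follow-up correlation 0.6, drop-out at random before month 1. It compares mean changes with single imputed values and, for MAR, completers only. It is a simple stand-in for the planned mixed model with multiple imputation. Cells give the mean estimate and, in brackets, the share of significant results.

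| Drop-out, intervention / control | MAR | LOCF | 2.5% per month | 5% per month |
|---|---|---|---|---|
| 20% / 20% | 0.099 (0.77) | 0.079 (0.76) | 0.079 (0.75) | 0.079 (0.73) |
| 25% / 15% | 0.101 (0.77) | 0.075 (0.71) | 0.071 (0.64) | 0.066 (0.56) |
| 30% / 10% | 0.101 (0.78) | 0.071 (0.66) | 0.062 (0.53) | 0.053 (0.37) |

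In the first row the rate has almost no influence. In the other two it has a clear one.

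**The case against.** - **The rate does matter when drop-out is unequal.** This stands. A reader might infer that the arm difference hardly moves whatever rate is chosen. The article does not support that, since it nowhere says drop-out will be equal. At 25% against 15%, going from LOCF to 5% per month cuts the share of significant results from 0.71 to 0.56.
- **The plan already shows some dependence on missing data.** This stands too. A reader might infer that the planned analyses cannot reveal whether the primary result depends on drop-out. But the MAR-to-LOCF contrast alone takes 0.118 to 0.094 at equal drop-out. Its limit is that it also treats both arms alike: with equal early drop-out, LOCF multiplies the MAR difference by one minus the drop-out share.
- **The added shift is modest.** With SE = 0.20 × √(2/60) = 0.037, a shift of 0.018 is about half a standard error, and it is smaller than the 0.024 between MAR and LOCF. That is fair. It is, however, a further loss on top of that contrast.
- **The threatening scenario is not documented.** The article expects missingness from worsening or new illness, which is not specific to an arm, and section {11b} expects only mild side effects. Nothing shows that intervention drop-outs will fare worse. That supports testing both directions; it does not show that a common decline is enough.
- **The common rate is inferred from silence, and an analysis plan not shown here could add to it.** True, although a single rate is the natural reading. The article itself fixes the approaches and the rates. The point is a better version of an analysis it specifies and does not depend on detail left to another document.

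**Conclusion.** The concern holds in limited form. As written, the decline scenarios add little beyond LOCF when the arms lose similar shares, and their agreement in that case says nothing about robustness. None of them examines informative drop-out that differs by arm. At 20% drop-out per arm, the untested intervention-only decline would remove 0.018 to 0.024 from an LOCF difference of 0.094, about a fifth to a quarter, where the planned version removes about 0.

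Those figures rest on an assumed mean index of 0.6 to 0.8, an assumed SD of 0.20 and an effect size carried over from another questionnaire. The near-zero shift under a common decline does not depend on the mean or SD; it requires similar drop-out shares and similar last values in the two arms.

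The primary analysis is not invalidated. This is an inexpensive improvement that should be made before the imputed results are used to support an effectiveness claim.

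**What to change.** Keep the three approaches and the stated rates. Add to section {20c}, or to the analysis plan:

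1. Arm-specific versions in both directions: 2.5% and 5% per month in intervention drop-outs with 0% in control drop-outs, and the reverse.
2. A tipping point: raise the decline in intervention drop-outs, with none in control drop-outs, until the primary 95% confidence interval first includes zero, and report that decline.
3. The drop-out share by arm beside these results, so that readers can see whether agreement among the common-decline scenarios carries information.

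This reuses the imputation code already planned and changes no data collection. The cost is a few extra runs, a sentence of text and one more table.

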#### Health-related quality of life

HRQoL is assessed using the EuroQoL EQ-5D-5L questionnaire [18, 19]. The questionnaire consists of five categories/questions including mobility, self-care, daily activities, pain/discomfort, and anxiety/depression. For each question, there are five possible answers each containing a score from 1 (no problems) to 5 (extreme problems). This will provide a combination of numbers [18] which is translated to a country-specific total index [36]. The lowest Danish index score is − 0.624 and the highest score is 1.000. In addition, the participant is asked to evaluate their own health on a scale from 0 to 100. A score of 100 means the best imaginable health [18].

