#### Sensitivity analysis

Additionally, linear mixed models that also include relevant covariates (as fixed effects) will be fitted to adjust for observed baseline imbalance (if needed). Relevant covariates include age, BMI, sex, pulmonary function, and the number of comorbidities.

For all fitted linear mixed models, the two estimated mean changes from baseline to 3 months (for both intervention groups) as well as the estimated mean difference in change from baseline to 3 months will be reported together with the corresponding 95% confidence intervals and *p* values. Statistical significance will be declared whenever the *p*-value is below 0.05.

Where appropriate, outcome values will be transformed prior to the statistical analysis.

For categorical secondary or other outcomes data will be analyzed by means of logistic mixed-effects regression models that include an intervention group-time interaction as a fixed-effects term and block and participant-specific random effects. Baseline values will be part of the outcome. The estimated difference in change from baseline to 3 months will be reported as a ratio of odds ratios together with the corresponding 95% confidence interval and *p* value.

Statistical analyses will be carried out using STATA/IC version 17.0 (StataCorp LP, USA). Specifically, the commands XTMIXED and XTMELOGIT will be used for fitting linear mixed models (using residual maximum likelihood estimation) and logistic mixed-effects regression models (using maximum likelihood estimation), respectively.

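### As described, the two effectiveness imputations fill in one fixed value per participant, so Rubin's rule adds no uncertainty, and none of the four versions is named primary

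*Protocol article*

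**What the plan says.** All of this is in the protocol article.

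- **Missing outcomes values {20c}, approach 1:** "HRQoL remains unaltered (corresponding to last observation carried forward").
- **Approach 2:** "HRQoL deteriorates over time with a rate of 2.5% or 5% per month to a maximum deterioration of 10 and 20%, respectively".
- **Approach 3:** mixed models on all available data without imputation, assuming data missing at random.
- **Uncertainty in approaches 1 and 2:** "For both approaches, multiple imputations will be applied to accommodate the uncertainty related to imputing missing data". The standard errors are to come from Rubin's rule.
- **Role:** "The two imputation approaches will produce estimates that may be used for evaluating effectiveness", whereas the available-case model is said to give efficacy estimates. Objectives {7} and Trial design {8} describe the trial's aim as effectiveness.
- **Scope:** "Intermittent missing outcome values occurring at the 1-month visit will not be imputed". The rules therefore act on participants without a 3-month value.
- **Decision rule (Sensitivity analysis, covering all fitted linear mixed models):** "Statistical significance will be declared whenever the" p-value falls under 0.05.
- **Scale (Health-related quality of life):** "The lowest Danish index score is" −0.624, and the highest is 1.000. A 0 to 100 own-health rating is also collected.

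**The concern.** Multiple imputation conveys uncertainty only if the imputed values differ between data sets. Carrying a value forward, or reducing it by a set percentage, gives the same number each time. No distribution around the rule and no random draw is described, so the stated method and its stated purpose do not fit together.

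The analyses concerned are not peripheral, because the section links them to the trial's objective. Counting the two deterioration rates separately, there are four versions of the primary analysis: carried forward, 2.5%, 5% and available-case. None is ranked first, and the same 0.05 threshold applies to each. A favourable result in any one could be presented as the result of the trial.

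Two smaller points sit in the same rule. The maximum deteriorations do not match a 3-month follow-up, and a percentage of an index that can be negative has no clear direction at or below zero.

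**Working it through.** **Inputs from the protocol article.** 60 per group and 20% drop-out (Sample size {14}); visits at baseline, 1 and 3 months (Participant timeline {13}); rates, maxima and Rubin's rule (Missing outcomes values). The sample size reproduces: 2 × (17 × (1.960 + 0.842)/10)² = 45.4, so 46 per arm; 46/0.8 = 57.5, so 58 against the stated 60. It is not affected by this point.

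**Assumed, because the article gives no figures.** Index SD 0.20, correlations between visits 0.6 to 0.7, half of the losses before month 1.

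**1. Rubin's rule.** Total variance T = W + (1 + 1/M)B, where W is the within-imputation variance, B the between-imputation variance and M the number of data sets. If the M data sets are identical, B = 0 and T = W. Illustration with M = 20, 60 per arm, SD 0.20, baseline-to-3-month correlation 0.6, 20% missing, last value at baseline:

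| Carried forward | W | B | T | SE |
|---|---|---|---|---|
| Fixed value | 0.000847 | 0 | 0.000847 | 0.029 |
| Same value plus a random draw (SD of observed changes) | 0.001057 | 0.000217 | 0.001057 + 1.05 × 0.000217 = 0.001285 | 0.036 |

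Over the three rules the fixed-value SE is 17 to 19% smaller. That gap is what the multiple-imputation sentence promises and the rules as described do not deliver.

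**2. Error rates under no effect.** Change scores, 60 per arm, simulated trials. At 20% missing, type I error was 5.2% for the carried-forward rule and 4.9% for each deterioration rule; at 30% missing it was 4.9 to 5.0%. For the carried-forward rule at 20% missing, the empirical SD of the estimate was 0.0306 and the mean SE 0.0307. Each test taken alone keeps its level. The chance that at least one of the four versions gives p < 0.05 was 6.4 to 7.7% over separate runs at 20% missing and 7.4 to 7.7% at 30%.

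**3. A true effect, data missing at random.** Take a true difference of 0.10, fully present by month 1, with 20% missing.
- Carried forward: 80% observed contribute 0.10, the 10% lost after month 1 contribute 0.10, and the 10% lost before month 1 contribute 0. The estimate is 0.8 × 0.10 + 0.1 × 0.10 + 0.1 × 0 = 0.09, which is 10% too small.
- 5% rule: 0.8 × 0.10 + 0.1 × 0.10 × 0.90 = 0.089.
- If no effect had emerged by month 1, carrying forward would give 0.8 × 0.10 = 0.08, which is 20% too small.

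Because the estimate is shifted, coverage falls slightly below 95%.

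**4. Maxima.** 3 months × 2.5% = 7.5% and 3 × 5% = 15% (compounded: 7.3% and 14.3%), against 10% and 20%. From a last value at month 1 the falls are 2 × 2.5% = 5% and 2 × 5% = 10%. Reaching the maxima takes 10/2.5 = 20/5 = 4 months.

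**5. Negative index, if the percentage multiplies the value.** At 15%: −0.20 × 0.85 = −0.17 and −0.624 × 0.85 = −0.530, both improvements; 0 stays at 0; 0.70 × 0.85 = 0.595, a fall.

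**The case against.** **The text does not say that fixed values are used.** It calls the approaches assumptions about participants with missing data, and the carry-forward wording could describe a mean trajectory with random draws around it. An analysis plan that is not shown may specify those draws. This stands in part: a zero-variance analysis is not proven. The mismatch is still on the page, because the section states both the rules and the variance method, and nothing stated links them.

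**A reader might infer that the filled analyses have invalid, too-narrow intervals.** In the set-up above, the carried-forward and deterioration SEs are about 0.84 to 0.85 of the available-case SE at 20% missing and 0.75 to 0.77 at 30%. Those ratios compare different estimators. Each filled estimate varies less, its SE tracks that variation, and its test holds 5% under the null. The documents do not support a claim of inflated error in any single analysis. The comparison also uses a completers' change score, not the planned mixed model with 1-month values.

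**Primacy could be read from the section headed Main analysis**, which names the linear mixed model; approach 3 is that model on available data, and the effectiveness sentence is permissive. This is fair, but Main analysis does not say how missing values are handled, and the later section links effectiveness to the other two approaches.

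**The smaller points are easily overstated.** The rates alone fix the imputed values, so unreachable maxima change no estimate. The negative-index problem depends on a percentage base that the text does not define, the 0 to 100 rating has no negative values, and the share of participants below zero is not given. Equal rates in both arms cancel only if drop-out and levels are similar, so an arm-specific decrement is a preference and not a correction.

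**Conclusion.** The concern holds as an internal contradiction joined to an unranked set of analyses. Under the rules as described, between-imputation variance is exactly zero, so Rubin's rule cannot carry imputation uncertainty unless an undescribed random component is added. This part needs no assumption about the data.

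The consequences are moderate. The chance of some significant result among the four versions is about 6 to 8% instead of 5%, and a true effect shrinks by about 10% at the planned 20% loss. Both figures rest on the assumed SD, correlations and timing of loss; the shrinkage also assumes data missing at random and an effect complete by month 1.

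The maxima are redundant but harmless to the estimates. The improvement of negative scores follows only if the percentage multiplies the index.

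**What to change.** 1. Name the mixed model on all available data from all randomised participants as the single primary analysis of HRQoL.
2. Label approaches 1 and 2 as sensitivity analyses. Implement them as delta-adjusted multiple imputation: draw missing 3-month values at random from an imputation model, subtract an absolute index decrement per month, and combine with Rubin's rule. An absolute decrement also removes the problem at and below zero. If fixed fills are kept, drop the claim that Rubin's rule captures the imputation uncertainty and define the base of the percentage.
3. State the decrement actually reached at 3 months in place of the 10% and 20% maxima.
4. Optionally, add a version with the decrement in the intervention arm only.

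The cost is wording, some code and wider intervals in the sensitivity analyses. No data collection or sample size changes. The choice should be fixed before any analysis by allocated group.

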#### Prognostic data

Information regarding oxygen therapy and exacerbations will be obtained from participants at 1- and 3-month follow-ups supplemented with information from patient files. Information regarding hospital contacts and mortality will be obtained from patient files.

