### Plans to promote participant retention and complete follow-up {18b}

From previous studies among individuals with severe COPD, it has been reported that it was a challenge to recruit participants due to the burden of their clinical condition [41]. Therefore, it is important to minimize the burden for the patients and to secure a comfortable atmosphere. This study intends to have as few outcomes as possible that require physical activity from the participant, few different persons involved in patient contact, and to do all assessments as home visits. We expect this will increase the likelihood of a higher recruitment and retention rate throughout the study period. The study coordinator will be involved in every contact with the participant to secure a familiar and comfortable atmosphere. In case the study coordinator is unable to attend, it is necessary that a replacement will be arranged in agreement with the participant. The potential replacement will receive thorough training. The study coordinator is therefore involved in every step from recruitment, throughout the course of the intervention and at all visits. Participants may withdraw from the study at any time. The study coordinator will make any reasonable effort to complete the follow-up. Participants who wish to withdraw will be asked if they want to withdraw completely or partially. Partial withdrawal may be either to accept the use of their data collected prior to withdrawal or to continue without any future contact i.e. only data collection via patient files.

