### Data collection for participants who discontinue or deviate from intervention protocols

Deviation from the intervention is defined as less than 6 regular contacts and an intake of less than 80% of the calculated protein or energy requirement for ≥ one third of the intervention period. Reasons for non-adherence will be registered as part of the regular contact or at follow-up visits. It is the intention to collect all data independent of deviation from the protocol.

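### The missing-data rules for hospital contacts and deaths do not exempt values still obtainable from patient files, and where values are truly missing they do not suit counts or events

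*Protocol article*

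**What the plan says.** **Source of the data.** Under Prognostic data: "Information regarding hospital contacts and mortality will be obtained from patient files". These outcomes do not depend on a home visit.

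**What drop-out means.** The eligibility section lists two drop-out criteria, loss to follow-up and withdrawal. On withdrawal, section 18b says: "Participants who wish to withdraw will be asked if they want to withdraw completely or partially". A partial withdrawal takes one of two forms: to "accept the use of their data collected prior to withdrawal", or "to continue without any future contact i.e. only data collection via patient files". The section on deviation from the intervention adds: "It is the intention to collect all data independent of deviation from the protocol".

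**Missing-data rules (section 20c).** "For the secondary outcomes, missing outcome values will be handled in the same way as the primary outcome". Under the first approach, "secondary outcomes remain unaltered after drop-out (corresponding to the last observation carried forward"). Under the second, most continuous secondary outcomes worsen by a fixed percentage per month, and hospital contacts have their own rule: "The secondary outcomes related to hospital contacts will increase over time by 2.5 and 5% per month to a maximum of 10 and 20%, respectively". Available-case analyses are also planned. The section expects missing data to arise mainly from worsening COPD, other comorbidities or newly found conditions.

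**Status of the outcomes.** The Outcomes section and Table 2 list hospital contacts, hospital days and mortality as secondary, followed to 3 months. Table 2 gives them no baseline entry.

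**The concern.** Two things do not fit together.

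First, the event that triggers carry-forward is drop-out, but ending home visits does not close the patient files. Nothing in the missing-data section says that the files are read first. An analyst who follows it could treat a participant lost at month 1 as missing for admissions and death, when both could be looked up.

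Second, a percentage change suits a continuous score. Applied to a count it cannot create an event where none has yet occurred. Applied to vital status, carry-forward can only return alive for someone last known alive. Since the protocol expects drop-outs to be getting worse, the rules assign few or no further events to the people most likely to have them.

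Admissions, hospital days and deaths are the prognostic results of the trial, and section 20c says that the imputed analyses may serve to evaluate effectiveness. Too few events among drop-outs would pull down the arm means. It would also distort the comparison if drop-out, or the event rate among drop-outs, differed between arms.

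**Working it through.** **1. Scale of drop-out.** The sample size section gives a difference of 10, SD 17, power 0.8, significance level 0.05 (two-sided assumed), 20% drop-out and 60 per group. The normal approximation gives 46 per arm, and 46/0.8 = 57.5, so 58. The t-test version gives 47, and 47/0.8 = 58.75, so 59. The stated 60 is reproduced closely. Expected drop-out is 0.20 × 120 = 24, or 12 per arm.

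**2. Where the files stay open.**

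| Participant | Files usable to 3 months? |
|---|---|
| Lost to follow-up, no refusal | Yes, on the protocol's own source of data |
| Partial withdrawal, file-only | Yes, stated |
| Partial withdrawal, earlier data only | No |
| Complete withdrawal | Presumably no |

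The protocol does not say how the 24 would divide among these rows.

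**3. The percentage rule on a count, from month 1 to month 3.** Two monthly steps multiply by 1 + 2 × 0.025 = 1.05 or 1 + 2 × 0.05 = 1.10 (1.051 or 1.103 compounded).
- A count of 0 stays 0 at either rate.
- A count of 1 becomes 1.05 or 1.10, which is not a possible count.
- The caps are reached after 10/2.5 = 4 months and 20/5 = 4 months. Even three full months give only 7.5% or 15%, so neither cap can apply in a 3-month trial.
- A drop-out before month 1 has no baseline value to carry forward.

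**4. How often the month-1 count is zero.** The documents give no contact rates, so the yearly rate λ is assumed. With a Poisson count, P(0) = exp(−λ/12): 96% at 0.5 per year, 78% at 3, 51% at 8 and 37% at 12. Zeros dominate for rarer events such as admissions, but not for frequent outpatient calls or visits.

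**5. Size for counts.** Assume a constant rate λ, all 20% drop out at month 1, no file data used, and the cumulative count carried forward.
- True 3-month mean for a drop-out: λ/4. Carried forward: λ/12.
- Ratio: (1/12)/(1/4) = 33%. With the rises it is 33.3% × 1.05 = 35%, or 33.3% × 1.10 = 37%.
- Arm mean, equal rates: true 0.25λ. Imputed 0.8 × λ/4 + 0.2 × λ/12 = 0.2167λ, which is 13.3% too low. With the 1.10 factor it is 0.2183λ, 12.7% too low.
- Arm mean, drop-outs at 2λ: true 0.2λ + 0.1λ = 0.30λ. Imputed 0.2λ + 0.2 × 2λ/12 = 0.2333λ, 22.2% too low. With the 1.10 factor it is 0.2367λ, 21.1% too low.

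The protocol does not say whether the carried count is cumulative. If the month-1 count were instead repeated for months 1 to 3, a drop-out would be given λ/12 + λ/12 = λ/6, which is 67% of λ/4. The arm mean at equal rates would be 0.8 × λ/4 + 0.2 × λ/6 = 0.2333λ, 6.7% too low.

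**6. Size for deaths.** Assume yearly mortality of 10% to 25%. The upper value is the Background's figure for the first year after discharge from a COPD hospitalization, used only for scale. The risk over months 1 to 3 is 1 − (1 − m)^(2/12), which is 1.74% to 4.68%. Among 24 drop-outs that is 0.4 to 1.1 deaths carried forward as alive if no file is read. Among all 120 over 3 months, 120 × [1 − (1 − m)^(3/12)] gives 3.1 to 8.3 deaths.

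**The case against.** The strongest reply is that the section governs missing values only. An admission or death found in a file is not missing, so nothing in the text orders it to be overwritten. Read with the sections on prognostic data, retention and deviation, imputation could fall only on participants whose files are closed, and some rule is needed for them. This stands. A reader might infer that the plan replaces recorded events with invented ones, or loses every death after drop-out; the documents do not say so. Events go unused only if drop-out is itself taken to make these outcomes missing. The carry-forward wording invites that reading without requiring it.

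Four further limits also stand.
- The percentage rise is stated for hospital contacts, not deaths. Mortality is reached only through the general carry-forward wording.
- The available-case mixed models do not discard a drop-out, because the month-1 record remains in.
- Admissions and deaths are not the only account of harm, since section 22 registers all adverse events.
- Treating all 24 drop-outs as having no file data is a worst case.

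Two replies do not succeed. One is that a files-first sentence is detail left to another document. Section 31c describes the article as the full protocol, and the point concerns rules it states, not ones it omits. The other is that multiple imputation, planned for both imputation approaches, repairs the zeros. It may add spread, but the stated assumption for a participant with no contacts is still none, and no distribution for counts is given.

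**Conclusion.** The concern holds in a limited form. The missing-data section does not exempt outcomes that the protocol takes from patient files and can still obtain for many drop-outs. For those whose later data are truly missing, the rules are unsuited to counts and to vital status, whichever way drop-out is read.

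Under the stated assumptions a drop-out's imputed count is about 33% to 37% of the true 3-month mean. The arm mean is about 13% too low, or 21% to 22% if drop-outs have double the rate. Repeating the month-1 count instead roughly halves the equal-rate error. For deaths the worst case is about one, small in number but not trivial against 3 to 8 expected. All these figures rest on assumed rates and on no file being read after drop-out, and they shrink as files are used. What remains with consistent file use is the smaller group whose files are closed. The primary outcome is not affected.

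**What to change.** In section 20c:

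1. State that hospital contacts, hospital days and mortality are taken from patient files to the fixed 3-month date for every randomised participant who has not refused file access, whether or not home visits continued.
2. Remove these outcomes from the carry-forward and percentage-rise rules.
3. For participants whose files are closed, censor at the withdrawal date and analyse observed time at risk: a count model with an exposure offset for contacts and days, and an event model for death.

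Censoring assumes that participants who close their files would go on at the same rate as comparable participants. If the authors want to keep a worsening scenario, a multiplied event rate after censoring does this without leaving zeros fixed at zero.

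The cost is file extraction for up to about 24 participants, from records the trial already uses, and a count or event model in place of the mixed models now planned for these outcomes. No extra patients or visits are needed.
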